## 7.6 Recruitment Procedure

### 7.6.1 Recruitment

Initially, recruitment will focus on internal referrals through hospital clinics at both The Children's Hospital at Westmead (Endocrinology and Weight Management clinics) and Monash. Following this initial recruitment, a range of strategies will be used including [56, 57] :

- Strong study branding and logo.
- Study website which will include study information for youth and parents, an expression of interest online form submission, direct phone and email contact details, links to other relevant resources and services.
- Information for patients on waiting lists at the participating clinics.
- A variety of communications to health professionals within the local area including GPs, paediatricians and dietitians.
- Youth-focused and parent-focused local media campaigns using media releases, radio, newspapers – via support of CHW and Monash PR Departments.
- Use of social media:
  - Existing Twitter feeds, institute and personal feeds (e.g. @MonashNutrition, [name]) may be used by research investigators in a professional manner to inform medical and health care professionals about the study and recruitment. For example 'Fast Track to Health, RCT of intermittent energy restriction vs. continuous energy restriction in adolescents with obesity NOW RECRUITING'
  - An active social media presence through a study page on Facebook will be established, containing basic information about the study with a primary objective of re-directing interested participants or parents to the study website. Interested participants or parents will be able to directly connect with the study through direct messaging from the Facebook page. The page will link directly to the Fast Track website where interested participants or parents will have the ability to complete an eligibility check and submit an expression of interest form.
  - The target audience for our Facebook page is: young people (13 – 17 years) living near the study site (either BASE at Monash University or The Children's Hospital at Westmead, parents of young people who may be eligible for the study and also health professionals who treat people who may be eligible for the study in the community.
  - To ensure our target audience is reached by the social media page, targeted Facebook ads will be used as a recruitment strategy:
    - Participants: a Facebook ad will target participants within the geographic area of each study site. Ads will be targeted based on age (13-17yrs), postcode, and areas of interest including weight loss and dieting.
    - Parents: a Facebook ad will target parents within the geographic area of each study site. Ads will be targeted based on age (35-55yrs), postcode, and areas of interest including parenting, weight loss and dieting.
    - Evaluations will be completed to assess the spread and reach of the Facebook advertisements. Page views will also be evaluated by age, gender, device used etc., using the Facebook 'Insights' tab.

Young people who have participated in weight loss studies have often enquired about enrolment after having seen promotional materials several times or in different locations. We will offer a range

of ways of enquiring about the study: website, text messages, email or mobile. These will be monitored to determine the most successful recruitment strategies. Ethics approval will be sought prior to the implementation of each recruitment strategy.

### 7.6.2 Retention strategies

Strategies to retain participants in the study include:

- Thank you, birthday and Christmas/ New Year greetings.
- Facility for updating contact details and recording details of two family members or close friends.
- SMS reminders for appointments.

We will also provide:

- Some flexibility in scheduling appointments.
- At least weekly contact between the study team and participants offering a variety of contact methods including face-to-face meetings, Skype, face-time, zoom, telehealth appointments, telephone calls, emails, or SMS text messages, depending on the participants preference.
- Timely feedback on healthy lifestyle changes and weight goals using a practical, supportive and flexible approach suited to this age group.
- Free parking (Monash) or parking vouchers (CHW) and a petrol gift card at each face-to-face visit to assist with travel costs.
- Gift Vouchers at 52 week appointments (\$20 Coles Myer gift card).
- Fitbit® wristbands (Fit Bit Flex 2) will be given to participants at week 16 to enhance motivation and engagement as contact with the dietitian decreases during the final phase of the study

## 7.7 Inclusion Criteria

- Adolescents aged 13–17 years (inclusive)
- Obesity (defined as equivalent to adult BMI 30–45 kg/m^2) [58] and at least one of the following metabolic complications:
  - o Pre diabetes: impaired fasting glucose 5.6-6.9mmol/L and/or impaired glucose tolerance 2 hour post load 7.8-11.1mmol/L
  - o Insulin resistance: fasting insulin (pmol/L)/glucose(mmol/L) ratio >20
  - o Presence of acanthosis nigricans
  - o Hypertension: systolic and/or diastolic blood pressure above the 90th percentile for sex, age and height
  - o Low HDL-C <1.03mmol/L
  - o High triglycerides ≥ 1.7mmol/L
  - o Abnormal Alanine Transaminase (ALT) or Gamma-Glutamyltransferase (GGT) based on standard PowerChart cut-points (i.e. ALT or GGT >45 U/L)
  - o Diagnosis of polycystic ovary syndrome (PCOS)

## 7.8 Exclusion Criteria

- Secondary obesity
- Significant intellectual disability as documented by the referring doctor
- Significant medical or psychiatric illness
- Previous diagnosis of Type 2 Diabetes Mellitus
- Currently undergoing treatment for a clinical eating disorder

- Pregnancy, or planning to become pregnant within the next 18 months
- Taking medications that have an effect on weight in the short term (excluding metformin)
- Adolescent or parent with poor level of spoken English
- Current enrolment in a weight loss program
- BMI in excess of 45kg/m^2

## 7.9 Screening Assessment

Screening assessments will be completed for all participants prior to enrolment. This may be completed as a standalone appointment or combined with the baseline visit.

The following must be done to confirm eligibility:

1. **Clinical assessment:** All participants will be assessed by a referring clinician or the study doctor.
2. **Biochemistry:** Fasting insulin, glucose, LFTs and lipids will be reviewed by the study doctor. At the on-site screening appointment all parents and adolescents will also be asked whether they consent to the adolescent's screening pathology results being used in analyses (irrespective of whether they are eligible to enrol).
3. **Blood Glucose Levels:** Trained personnel may also measure blood glucose levels via a finger prick blood sample using the Freestyle Optium Neo Blood Glucose and Ketone meter. This is to identify participants who may have undiagnosed Type 2 Diabetes. Participants will be excluded from the study if:
  - a. Fasted blood glucose >7mmol/L
  - b. Random blood glucose >11.1mmol/L
4. **Screening questionnaires:** The EDE-Q and CESDR-10 will be used to screen participants for eating disorders and depression. The questionnaires will be completed prior to enrolment in the study and are repeated at weeks 4, 16 and 52. Screening questionnaires are emailed to potential participants prior to attending an on-site appointment. At the on-site screening appointment all parents and adolescents will also be asked whether they consent to the adolescent's screening questionnaire data being used in analyses (irrespective of whether they are eligible to enrol). Should a participant complete screening questionnaires without attending an on-site appointment to provide consent, data collected will not be included in analyses.
5. **Psychological assessment:** A psychologist may be involved in participant assessment prior to enrolment. This will be based on screening questionnaires and input from the study doctors or dietitians.

**Please note:** If a recent blood test (taken in the previous 8 weeks) is available, this will be used to confirm eligibility. Alternatively, a fasting blood sample may be collected by trained personnel prior to a participant's enrolment in the study. This will include collection of bloods for storage. A consent form must be signed prior to the collection of fasting bloods. Stored blood samples collected for individuals who do not progress to enrolment will be destroyed immediately.

If the inclusion and exclusion criteria are met to the satisfaction of the reviewing practitioner/s, the participant will be enrolled into the study. Ineligible participants will be asked if they would like to be contacted by investigators in the future if suitable studies arise that may be of benefit to them.

## 7.10 Consent

The investigator is responsible for obtaining a participant's written informed consent to participate in the study from parent(s)/guardian(s). The Information Sheet and Consent Form prepared for the study complies with the provisions of ICH GCP and local legal requirements. To be able to engage in the consenting discussions, children <18 years of age will be provided with Information Sheet Only. Before undergoing screening procedures for possible enrolment into the study, participants/families must be informed, in an understandable form, about the nature, scope, and possible consequences of the study. This information must be given orally to participants by a physician or Accredited Practising Dietitian (according to applicable regulatory requirements) who is well informed about the nature, scope, and possible consequences of the study. Written information about the study will also be provided in a Participant Information Sheet. The date on which this oral and written information on the study was provided to the participant, and by whom it was provided, must be documented in the information Sheet and Consent Form.

## 8 Participant Safety and Withdrawal

### 8.1 Risk Management and Safety

There are no identified risks for participants as the study is relatively low risk with no invasive procedures and drug therapy. The study is being conducted by well trained and GCP accredited study personnel. Data generated from this study will only be presented as pooled results therefore, the confidentiality of participants will always be protected in dissemination of these research results. No individual participant will be able to be identified from publications and presentations arising from this study.

### 8.2 Adverse Event Reporting

#### 8.2.1 Definitions

An adverse event is any undesirable sign, symptom or medical condition occurring after starting the study therapy (the IER diet). A medical condition/disease present before starting the study treatment will only be considered an adverse event if it worsens after starting the study treatment.

Pregnancy will be reported as an adverse event and followed to determine the outcome. Any study participant who becomes pregnant during the study will be withdrawn from the study.

A serious adverse event is an undesirable sign, symptom or medical condition which,

- (1) is fatal or life-threatening,
- (2) requires admission to hospital as an inpatient,
- (3) results in persistent or significant disability/incapacity,
- (4) constitutes a congenital anomaly or birth defect,
- (5) is medically significant, may jeopardize the participant and may require medical or surgical intervention to prevent one of the outcomes listed above.

A SUSAR is a serious adverse event that is suspected to be related to the study but unexpected.

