## 5.2 Introduction

One in four Australian adolescents has overweight or obesity, with prevalence rates continuing to rise. Effective treatment of obesity in this age group is vital. Dietary interventions are generally effective in treating obesity in the short term, but the best way to achieve weight loss longer term in adolescents is unknown. Young people with obesity find it very difficult to adhere to the routine of daily calorie restriction - a core element of current weight management programs.

A new diet intervention that has demonstrated success in adults is intermittent energy restriction (IER), a variant of which is the diet popularised as the “5:2 Diet”. There are many variations of IER in the literature, approaches typically involve 2-6 days per week of intense energy restriction (i.e. consuming 25-35% of daily energy needs) alternated with days of healthy eating or ad libitum intake

Despite the current research interest in IER in adults, there have been no studies of its use in adolescents. There are potential safety concerns as to whether IER promotes the development of disordered eating and whether it is nutritionally adequate. However, the avoidance of every day calorie restriction, the overall lower energy intake that IER provides, and its flexibility in terms of youth lifestyles makes IER potentially very appealing, and hence sustainable to adolescents. This study is the first randomised controlled trial (RCT) of IER in adolescents.

This study is a multisite RCT weight-loss intervention comparing IER with a standard hypocaloric diet in adolescents aged 13-17 years with obesity.

The study *challenges existing clinical paradigms* by proposing that IER can be implemented as an alternative to standard continuous energy restricted diets for adolescents with obesity.

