## 7.2 Study Type & Design & Schedule

### 7.2.1 Study Design

This is a prospective, randomised, multi-centre study designed to determine if IER results in lower BMI z-score after 52 weeks of intervention in adolescents with obesity, compared with a standard, usual care, hypocaloric dietary intervention. A total of 186 participants aged 13–17 years will be randomised on a 1:1 ratio to 4 weeks of VLED, followed by 48 weeks of IER (experimental arm), or 4 weeks of VLED, followed by 48 weeks of current best-practice calorie restricted diet (active control arm). To ensure even distribution, randomization will be stratified by clinical study site, age, sex and BMI. Randomisation will occur at baseline and participants will be informed of their allocated dietary patterns during phase 1.

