### 7.2.2 Study Description

There are three phases in the intervention:

1. Jump-start weight loss
2. Intensive diet, and
3. Step-down diet

All participants will undergo an initial VLED jump-start phase (up to 4 weeks) and then transition to a standard dietary intervention (active control) or IER (experimental arm). The VLED jump-start phase achieves rapid, short-term weight loss, compared to commencing intensive diets immediately, and is frequently used in clinical practice. Short term weight loss predicts long term weight loss success[10], but VLEDs are severe diets and may not be sustainable long term.

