#### 8.2.2 Assessment and Documentation of Adverse Events

Monitoring of relevant clinical and laboratory safety parameters will be undertaken by researchers at the time of each visit.

Any adverse event will be assessed and managed by the participant's physician, or general practitioner, with the event followed to resolution. Conditions that are present at screening and do not deteriorate will not be considered adverse events. Abnormal laboratory values will not be adverse events unless deemed clinically significant by the investigator and documented as such. Changes in the severity of an adverse event will be reported. Adverse events characterised as intermittent will be documented for each episode. All adverse events will be followed to adequate resolution, where possible.

Any serious adverse event will be reported in writing to the relevant HREC within 72 hours of the event. The description of each adverse event on the CRF will include:

- A description of the adverse event;
- The onset date, duration, date of resolution;
- Severity (mild, moderate or severe);
- Seriousness (i.e. is it an SAE?)
- Any action taken (e.g. treatment, follow-up tests);
- The outcome (recovery, death, continuing, worsening);
- The likelihood of the relationship of the adverse event to the study treatment (unrelated, possible, probable, definite).

The seriousness of an adverse event will be assessed by an investigator according to the definition stated above in this section, with the following exception:

Hospitalisation due to progression of disease will not be considered a serious adverse event for the purpose of this study.

Adverse events due to the study (rather than the clinical procedure) are not expected to occur. Where study results suggest patterns of adverse events related to clinical care, study personnel will discuss concerns with clinical teams in a timely manner.

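### The adverse event definition starts at the IER diet, so read literally it omits non-serious control-arm events and VLED-phase events in both arms, and an adverse event comparison built on it is one-sided

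*Protocol*

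**What the plan says.** Section 8.2.1 (Definitions) states: "An adverse event is any undesirable sign, symptom or medical condition occurring after starting the study therapy (the IER diet"). The parenthesis equates study therapy with IER. On pre-existing conditions the same section adds: "A medical condition/disease present before starting the study treatment will only be considered an adverse event if it worsens after starting the study treatment". Section 8.2.2 uses a different reference point: "Conditions that are present at screening and do not deteriorate will not be considered adverse events".

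The serious adverse event definition, also in 8.2.1, is separate. It opens "A serious adverse event is an undesirable sign, symptom or medical condition which" and then lists criteria, with no mention of IER and no start point.

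On design, section 7.2.1 has participants "randomised on a 1:1 ratio to 4 weeks of VLED, followed by 48 weeks of IER (experimental arm"), or to "4 weeks of VLED, followed by 48 weeks of current best-practice calorie restricted diet (active control arm"). Section 7.2.2 confirms the order: "All participants will undergo an initial VLED jump-start phase (up to 4 weeks) and then transition to a standard dietary intervention (active control) or IER".

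Section 7.2.6 has the investigator establish at every clinical visit whether adverse events have occurred. Section 8.2.3 has every participant asked about health problems at every visit and adverse events entered in case report forms. Neither section restricts this by arm or by phase.

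**The concern.** Control participants never start IER, so the condition that opens the definition is never met for them. IER participants meet it only when the VLED phase ends. A site that follows 8.2.1 to the letter would therefore record non-serious events in one arm only, and would record nothing non-serious during the VLED, a diet that section 7.2.2 itself calls severe.

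Safety is a question the trial sets itself. The lay summary (5.1) says the study will test whether IER is safe, and section 5.2 says: "There are potential safety concerns as to whether IER promotes the development of disordered eating and whether it is nutritionally adequate". An adverse event table built on the literal definition would set the IER arm against an empty control column. IER would look worse by construction, and harm from the VLED common to both arms would go uncounted. A second risk is that two sites could record differently, one by the definition and one by the visit procedures, and each could point to the protocol in support.

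**Working it through.** The plan gives no figure for this point. The check is a reading of the sections side by side, followed by a count of how much planned follow-up the literal wording covers.

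**Step 1: definition against design**

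| Period and arm | IER started? | Within the literal definition? |
|---|---|---|
| VLED phase, experimental arm | No | No |
| VLED phase, control arm | No | No |
| After the VLED, experimental arm | Yes | Yes |
| After the VLED, control arm | Never | No |

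**Step 2: definition against the visit procedures.** Section 7.2.2 schedules face-to-face contact at weeks 0, 1 and 4. For a participant still on the VLED at the week 1 visit, the determination required by 7.2.6 could produce no non-serious adverse event in either arm, apart from pregnancy, which 8.2.1 makes reportable separately. Sections 7.2.6 and 8.2.3 clearly expect events to be looked for at these visits.

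**Step 3: pre-existing conditions.** Take a symptom that first appears in week 2 of the VLED and stays unchanged. It was absent at screening, so 8.2.2 does not exclude it. It was present before IER began, so 8.2.1, with study treatment read as IER, does exclude it. The two sections give opposite answers for the same event.

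**Step 4: extent.** Inputs: 186 participants randomised 1:1 (7.2.1), so 93 per arm; 52 weeks; 4 weeks of VLED (7.2.1). The 186 agrees with section 9.2: 130 / (1 − 0.30) = 185.7, rounded up to 186. Attrition is ignored.

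- Total planned time: 186 × 52 = 9,672 participant-weeks.
- Control arm, all outside: 93 × 52 = 4,836.
- IER arm during the VLED, outside: 93 × 4 = 372.
- Outside in total: 4,836 + 372 = 5,208, and 5,208 / 9,672 = 53.8%.
- Covered: 93 × 48 = 4,464, and 4,464 / 9,672 = 46.2%, all in the IER arm.

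The VLED lasts up to 4 weeks, and 7.2.2 allows an early move to the allocated diet. As the VLED shortens towards zero, the share outside falls towards 4,836 / 9,672 = 50%. The range is therefore 50% to 53.8%.

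**Step 5: effect on a comparison.** Suppose both arms have the same true rate of non-serious events, r per participant-week. The literal definition would yield an expected 4,464r events in the IER arm and none in the control arm, although the true expected number is 4,836r in each.

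**The case against.** The strongest reply is that the parenthesis is a drafting slip which no sensible site would follow. Everyone is asked about health problems at every visit, 8.2.2 looks back to screening, and no event-rate comparison is listed among the outcomes in 6.3. The concerns raised in 5.2 are also addressed by other means. The eating disorder, binge eating and eating behaviour questionnaires are scheduled for all participants at baseline and weeks 4, 16 and 52 (7.3 and Table 2), so they include the end of the VLED phase. Diet assessment and biochemistry are scheduled in both arms.

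Much of this stands, and it limits the consequences. It does not remove the defect. What 7.2.6 and 8.2.3 require to be recorded is adverse events, and 8.2.1 is where that term is defined. Asking both arms the same question does not ensure that both sets of answers are recorded.

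Three stronger readings are tempting, and the protocol does not support them.

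- A reader might infer that the arms cannot be compared on safety at all. Questionnaires, biochemistry, safety withdrawals and serious adverse events all cover both arms.
- A reader might extend the gap to serious adverse events, because 8.2.2 treats seriousness as an attribute of an adverse event. That link is arguable, but the serious event definition carries no IER condition, and 7.2.6 speaks of serious events during the study without restriction.
- A reader might infer that the oversight committee and the stopping rule rest on the defective counts. Section 8.2.2 gives the committee serious event reports and psychological questionnaire data, and the stopping rule counts investigator withdrawals for safety across the whole sample. Neither uses a count of non-serious adverse events.

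**Conclusion.** The adverse event definition is wrong as written. This is a stated rule that gives a wrong result if followed, not detail left for a later document. Taken literally, it excludes non-serious control-arm events and VLED-phase events in both arms, between 50% and 53.8% of planned participant-weeks, and leaves the IER arm as the only source of countable events. It also contradicts the visit procedures in 7.2.6 and 8.2.3 and the screening reference in 8.2.2.

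The percentages assume 93 per arm, 52 weeks of follow-up, at most 4 weeks of VLED and no attrition. They measure the reach of the wording. They are not evidence that data have been lost, because the document does not show how sites applied it. The damage is confined to adverse event recording and any comparison built on it.

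**What to change.** Amend section 8.2.1 in three respects:

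1. Delete the parenthesis that equates study therapy with the IER diet.
2. State that adverse events are counted in both arms from one common start point, for example randomisation, which 7.2.1 places at baseline when the VLED phase begins.
3. Choose one reference point for pre-existing conditions and use it in both 8.2.1 and 8.2.2.

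Removing the parenthesis also allows the relationship-to-treatment item in 8.2.2 to be completed meaningfully for control participants.

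The cost is a few sentences of amendment. No visit, procedure or question is added, since 7.2.6 and 8.2.3 already have events sought from all participants. The only downside is that more events will be recorded.
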